## Assignment of interventions: blinding

### Who will be blinded {17a}

Only the first author and another two members of the central project team who run the trial on a daily basis will be aware of when each site is crossing over to synoptic reporting. Hospitals will be aware what reporting method they are implementing. All other chief investigators and data collectors will be blinded as to when they are due to commence synoptic reporting. They will not be part of the process in which relevant personnel will develop the randomisation sequences for various batches of trial sites, and the randomisation schedule will be kept confidential from them. Data analysts will be informed of the planned time of switching of hospitals, but will not be informed of hospital names.

### Procedure for unblinding if needed {17b}

Hospitals will be aware when they have been switched over to the synoptic reporting, so no procedure for unblinding is necessary.

## Data collection and management

### Plans for assessment and collection of outcomes {18a}

Working together with the site clinicians/key contacts, the SCANPatient Central team will collect/extract baseline, post-operative, and survival data from various sources, including the MDM summaries, CT scan report, operation report, and pathology report. This will provide details of all treatment including surgery.

The main data required, sources, methods, and timepoints to collect them are summarised in Table 3.

The satisfaction of radiologists and hepatopancreaticobiliary (HPB) surgeons involved in the SCANPatient trial with respect to their use of standard reporting and synoptic reporting will be assessed using an online Clinician Satisfaction Survey developed by the SCANPatient research team (see Appendix 1).

### Plans to promote participant retention and complete follow-up {18b}

The SCANPatient central team will work closely with the site teams to make the processes as easy and smooth as possible. Central team plans to (1) follow up periodically to make sure that sites are sending documents as planned; (2) create detailed instructions and training materials for sites to use relevant platforms; (3) communicate with IT of the sites to allow them to enable access; and (4) provide standard templates of annual reports for the site to use, etc.

### Data management {19}

The SCANPatient Project team will extract required data from the main sources and enter them into the study REDCap database. During the synoptic report period, radiologists at each participating site will complete the synoptic report and enter relevant information directly into a module of the central REDCap database. Relevant data from the sites will be securely transferred to the central team via MDrive or REDCap. The data manager will regularly create reports to check data completeness and quality, follow up sites for missing data, and undertake data quality checks. All data will be stored using encrypted, secured, and regulatory-approved platforms and methods.

### Confidentiality {27}

There is an adequate plan to protect the confidentiality of data. Measures and safeguards we take to ensure the confidentiality and privacy of data are included in the SCANPatient data management plans, for both identifiable data (Appendix 2) and de-identifiable data (Appendix 3). To maintain the confidentiality of the data, access to identifiable information will be restricted to the minimum needed number of people in the project team and participating site clinicians. The REDCap software to be used for data collection allows for differing user access rights and will be set up so that clinicians can only view patient information from their own site. Personal medical information will always be treated as confidential, according to local privacy laws.

The trial will be conducted in compliance with the protocol; good clinical practice guidelines; university research procedures; relevant Commonwealth and State-based legislations and principles governing privacy and confidentiality. All information will be handled in accordance with Australian or equivalent privacy laws.

### Plans for collection, laboratory evaluation, and storage of biological specimens for genetic or molecular analysis in this trial/future use {33}

N/A. No such biological specimens will be collected in this trial.

## Statistical methods

### Statistical methods for primary and secondary outcomes {20a}

Results will be reported according to the CONSORT extension for stepped wedge trials [17]. Baseline data will be presented in a tabular form with mean and standard deviation or median with lowest and highest values, or percentages and counts as appropriate, by treatment group. We will also present baseline data by hospital and time period.

Results will be compared between *standard reporting* and *synoptic reporting* phases. All available primary and secondary outcomes will be analysed at the patient level using mixed-effects regression models with random intercepts for each cluster in each period, assuming a discrete time decay within-cluster correlation structure (where possible), a fixed effects for the intervention and separate fixed effects for period within each batch [15], or binary outcomes, log-binomial models will initially be fitted; should these fail to converge, mixed-effects Poisson regression models will be fitted, with robust variance estimation. Results will be presented as relative risks with 95% confidence intervals, and as risk differences with 95% confidence intervals. The sensitivity of results to the assumed within-cluster correlation structure will be assessed by fitting models with random effects for each cluster only, and for each cluster-period within cluster. Estimated intracluster correlations and cluster autocorrelations will be reported. The survival outcome will be analysed using a Cox proportional hazards model including shared frailty terms for cluster. All tests will be two-sided. Analyses will be conducted in Stata v 17 or later or in R version 4.2.1 or later as appropriate.

A statistical analysis plan will be prepared and finalised prior to the dataset being released to the statistician.

### Interim analyses {21b}

No interim analyses will be conducted.

### Methods for additional analyses (e.g. subgroup analyses) {20b}

To assess whether there is evidence of the effect of synoptic reports changing over time, an additional analysis including an interaction between the intervention term and time since synoptic reports were introduced in each site will be conducted for the primary outcome.

### Methods in analysis to handle protocol non-adherence and any statistical methods to handle missing data {20c}

Given that the proportion of missing data for the primary outcome is expected to be small, the main sensitivity analysis for missing data on the primary outcome will involve imputing data under two scenarios: “worst-best” and “best–worst” scenarios. In the “worst-best” scenario, missing data for diagnosis in the intervention arm will be imputed as “not borderline resectable”, while missing data in the control arm will be imputed as “borderline resectable”. In the “best–worst” scenario, the imputation will be reversed. The primary outcome will be analysed as described above under each of these scenarios. If these two scenarios lead to different conclusions regarding the treatment effect, a multiple imputation approach to dealing with missing data for the primary outcome will be taken.

### Plans to give access to the full protocol, participant-level data, and statistical code {31c}

The datasets used and/or analysed during the current study can be made available by the corresponding author upon request and in agreement with the research collaboration and data transfer guidelines of Monash University.

## Oversight and monitoring

### Composition of the coordinating centre and trial steering committee {5d}

A Trial Management Committee (TMC) and three subcommittees (an Operations Subcommittee, a Clinical Reference Group and a Consumer Reference Group) have been formed to oversee various aspects of the study. These project teams meet regularly to discuss various issues and monitor study progress, and any technical or safety or compliance issues that may jeopardise the completion or integrity of the study. They ensure that project reporting and milestones are met in a timely manner.

Details of the composition, roles, and meeting frequency of each of SCANPatient trial committees/subcommittees are summarised in Table 4.

**Table 4 Tab4:** The composition, roles and meeting frequency of SCANPatient trial committees and subcommittees

Name of committee/subcommittee	Composition	Main roles and responsibilities	Meeting frequency	Additional notes
Trial Management Committee (TMC)	The TMC is made up of all CIs and AIs, as well as a consumer representative	The role of the TMC is to oversee all aspects of the study (the operational elements of which will be delegated to the Trial Operations Sub Committee—see below) including liaison with partner organisations, risk management, training in the use of the synoptic tool and associated database, site recruitment including key link staff at each institution, management of the study throughout the recruitment period and subsequent analysis and reporting	The TMC meets at least quarterly in the first 12 months to ensure appropriate set-up processes are in place, and thereafter at a minimum of every 6 months unless required to meet more often	A Trial Management Committee (TMC) was formed at the outset of the grant (2021)
Trial Operations Subcommittee	It consists of all centrally employed personnel appointed to the study (including SCANPatient Fellow&Senior Research Officer&Data Manager), and the Upper Gastrointestinal Cancer Registry Program Manager, and CIA, CIJ, CII	In addition to the operational responsibilities referred to above, its role will be to prepare a formal protocol, obtain Ethics and Governance approval at the lead sites (Monash Health and Monash University) as well as at other sites as required, establish a central REDCap database accessible to all participating sites for entry of synoptic reports, site and central data management; and in conjunction with the statistical team develop electronic case record forms (eCRFs) for collection of short and longer term clinical data including baseline demographics as well as treatment and outcome data	It meets fortnightly at the outset, and more often when required	It was formed in August 2022
Consumer Reference Group	It is an eight-member group chaired by a consumer and attended by representatives of two pancreatic cancer patient groups—PANCARE and PANKIND, with additional representation from the AGITG (Australasian Gastrointestinal Trials Group) community advisory panel	The consumer reference group considers the communications strategy from a consumer perspective. The group has helped develop an appropriate ethics and governance framework, the trial opening announcement and, depending on results, will consider communication around how best to mainstream practices across the country	It meets at least yearly formally and more frequently when needed	It was formed in September 2022
Clinical Reference Group	This reference group is chaired by CIA and CIB and consists of 12 radiologists, surgeons and medical oncologists	The clinical reference group which takes responsibility for fine-tuning any of the details of the synoptic reporting and/or logistics from a radiological and surgical perspective as well as the implementation of these reports into day-to-day practice and the satisfaction survey This reference group will develop the tools to assess the satisfaction of clinicians regarding the implementation and use of the synoptic report, as well as some related substudies	It meets at least quarterly in the first 12 months, and thereafter at a minimum of every 6 months unless required to meet more often	It was formed in August 2022 This reference group helped develop the Clinician Satisfaction survey (see Appendix 1)

### Composition of the data monitoring committee, its role and reporting structure {21a}

N/A. No formal data monitoring committee has been established.

### Adverse event reporting and harms {22}

Patients in this trial are not having their care pathway altered in any way. The trial aims to improve the documentation of the CT scan review by using the synoptic report method which will not result in adverse events.

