## Introduction

### Background and rationale {6a}

Approximately 4000 Australians are diagnosed with pancreatic cancers annually, over 80% of which are pancreatic ductal adenocarcinoma (PDAC) [1, 2]. Despite recent advances in treatment, overall survival in people with PDAC remains poor, with a 5-year survival across all stages of only 11% [2]. With no screening test for early detection of PDAC currently available [3], there is an urgent need to improve these outcomes particularly as it is predicted that PDAC will become the second most common cause of cancer death by the end of this decade [1–3]. Between half and two-thirds of patients present with metastatic disease at diagnosis [1–3]. Of those without obvious metastases at diagnosis, tumours are assessed as to their resectability according to the degree of major vascular involvement by the tumour [3]. Conventionally, major arterial resection has not been performed during pancreatic resections due to concerns about operative and oncologic risks. As such, non-metastatic disease may be categorised as (1) locally advanced (LA) and therefore initially unresectable without major vascular reconstruction; (2) borderline resectable (BR) due to some degree of vascular involvement; or (3) clearly resectable (CR) based on no major vascular involvement [3].

Stratification into LA, BR and CR which determines optimal treatment (Fig. 1) requires high-quality, cross-sectional radiological imaging using computed tomography (CT) using a dedicated “CT pancreas protocol” [3]. Magnetic resonance imaging (MRI) scans may also be used to help discriminate the extent of localised disease but CT is the current “gold” standard. The respective percentages of tumours in each of these categories (CR, BR or LA) in any given cohort around the world are uncertain [4], given differing published definitions of each subtype, as well as known variation in the interpretation of CT scans by radiologists and pancreatic surgeons [5]. For example, in radiologic staging, the following factors may contribute to variability: scanner (e.g. image quality, specific protocols or contrast timing); accuracy of findings (radiologist awareness and experience); documentation of findings (clarity and completeness); context (timing of scans vs cytologic diagnosis); and synthesis (determining status from finding) [6].

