***Secondary***			
Patients diagnosed with CR PDAC	To determine the change in the proportion of patients with CR in a prospective cohort of patients with PDAC	SCANPatient REDCap Database	At the time of each patient’s assessment
Patients diagnosed with BR PDAC	To determine the change in the proportion of patients with BR in a prospective cohort of patients with PDAC	SCANPatient REDCap Database	At the time of each patient’s assessment
Patients diagnosed with LA PDAC	To determine the change in the proportion of patients with LA in a prospective cohort of patients with PDAC	SCANPatient REDCap Database	At the time of each patient’s assessment
Patients with CR PDAC planned to receive neoadjuvant chemotherapy	To determine the change in the proportion of patients with CR PDAC planned to have neoadjuvant chemotherapy	MDT summary	At the time of the MDT
Patients with BR PDAC planned to receive neoadjuvant chemotherapy	To determine the change in the proportion of patients with BR PDAC planned to have neoadjuvant chemotherapy	MDT summary	At the time of the MDT
Patients with LA PDAC planned to receive neoadjuvant chemotherapy	To determine the change in the proportion of patients with LA PDAC planned to have neoadjuvant chemotherapy	MDT summary	At the time of the MDT
Patients undergoing R1 resection	To determine the change in the proportion of patients undergoing R1 resection (microscopic margin positivity)	SCANPatient REDCap Database	At the time of surgery (if undertaken)
Patients undergoing R2 resection	To determine the change in the proportion of patients undergoing R2 resection (macroscopic margin positivity)	SCANPatient REDCap Database	At the time of surgery (if undertaken)
Patients surgery is abandoned	To determine the change in the proportion of patients whose surgery is abandoned intraoperatively	Surgical operation report	At the time of surgery (if undertaken)
Patient’s management strategy changed	To determine the change in the management strategies for patients with CR, BR and LA PDAC	MDT summary	At time of MDT
Patients with CR PDAC survival status	To determine the overall survival rate for patients with CR localised PDAC	Sites and the national death registry	6 months post completion of recruitment at end of trial
Patients with BR PDAC survival status	To determine the overall survival rate for patients with BR localised PDAC	Sites and the national death registry	6 months post completion of recruitment at end of trial

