Patients with LA PDAC survival status,	To determine the overall survival rate for patients with LA localised PDAC	Sites and the national death registry	6 months post completion of recruitment at end of trial
Satisfaction of specialists with synoptic report	To determine the satisfaction of radiologists and HPB (hepatobiliary) surgeons involved in this trial	Health service survey	Prior to the introduction of synoptic reporting and 6 months post commencing synoptic reporting
Synoptic report used routinely as standard of care	To determine the extent to which the synoptic reports for PDAC has become standard of care in routine MDT meetings and whether this model has been incorporated into in-house RIS/PACS (radiology information systems and picture archiving and communication systems)	Health service survey	6 months after trial complete

We hypothesise that the introduction of the synoptic radiological template report will alter (increase) the rate of diagnosis of BR PDAC from baseline.

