### Relevant concomitant care permitted or prohibited during the trial {11d}

Not relevant, this study relates only to the discussion and planning phase of treatment and there will be no impact on concomitant or future care subsequent to the MDM presentation.

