### Sample size {14}

Currently 8% of all patients diagnosed with PDAC are categorised with BR disease in the Upper Gastrointestinal Cancer Registry (UGICR; unpublished data) which is operating in most major centres in Victoria and approximately half of the major centres in New South Wales. We hypothesise that with the introduction of a new structured radiology report, leading to increased diagnostic accuracy, this will increase to 15%. This is supported by the final results of the pilot synoptic report study (wherein the rate of BR disease was 13% in the pilot study across 95 patients [12]) and international registry data which have shown that the rate of resection of major vascular structures at the time of surgery for PDAC is between 10 and 15% [14], a surrogate for involvement of those major structures and therefore a pseudo-definition of BR disease. As not all patients with BR PDAC will require formal venous or arterial resection, it is likely the actual rate of BR disease is higher in these larger international and national registries. An increase in the diagnosed rate of BR disease to this level will result in more patients appropriately being given neoadjuvant therapy, and a clinically meaningful change in the standard of care if identified.

The trial was originally designed as a standard, stepped wedge design with 8 hospitals randomised to each sequence of a standard 5-sequence/6-period stepped wedge design (a total of 40 hospitals). With 15 patients per hospital in each 6-month period, assuming a two-sided significance level of 0.05, this design has power ≥ 80% to detect an increase from 8 to 15% in the primary outcome. Power is maintained for a wide range of intracluster correlations and alternative within-cluster correlation structures, e.g. for a discrete time decay within-cluster correlation structure [15], with an intracluster correlation of 0.1 and a cluster autocorrelation of 0.55, power is 84%. Under most within-cluster correlation structure assumptions, power will remain > 76% should hospital recruitment be up to 25% lower and patient recruitment up to 30% lower than expected (i.e. with 10 patients each year in each of 30 hospitals). With the batched variant shown in Table 2, for the extreme scenario considered above (an intracluster correlation of 0.1 and cluster autocorrelation of 0.55), power levels remain > 80%. Sample size calculations were performed using the Shiny CRT calculator [16].

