## Discussion

Better classifying patients with non-metastatic PDAC as having tumours that are either clearly resectable, borderline resectable, or locally advanced and unresectable may improve patient outcomes by avoiding ineffective surgery, optimising care and treatment planning. The borderline resectable group are a small but important cohort in whom surgery with curative intent may be considered; however, inconsistencies with definitions and an understanding of resectability status means these patients are often incorrectly classified and hence overlooked for curative options.

The SCANPatient trial has built on a small-scale pilot study [12] and is now expanding the synoptic reporting approach to over 30 major hospitals across Australia. As the requirements and procedures of research ethics and governance applications (as well as the research management systems) in different states/jurisdictions and types of hospitals vary (e.g. public vs private hospitals, health services with or without radiological/MDM capacity), this multi-centred and stepped wedge clinical trial has its challenges in implementation. After some delays in site governance approvals, data collection finally started from early July 2023.

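### Overall survival is listed only within resectability labels that the synoptic report is meant to change, so any within-label survival comparison between phases is open to stage migration

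*Protocol article*

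**What the plan says.** **Survival.** Table 1 (Objectives {7}) has three survival rows, one per category. The BR row reads "To determine the overall survival rate for patients with BR localised PDAC" and the LA row "To determine the overall survival rate for patients with LA localised PDAC"; the CR row has the same form. No row covers all patients.

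**Labels.** The hypothesis below Table 1 is that the report raises the rate of BR diagnosis. Sample size {14} plans for a rise from 8% to 15% of all patients with PDAC.

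**Analysis.** Statistical methods {20a} says that results are compared between the standard and synoptic phases. It gives all primary and secondary outcomes a mixed-effects model with fixed effects for period within batch. A separate sentence gives survival a Cox model with shared frailty for cluster. That sentence names no population and no period effects.

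**Effect on care.** Adverse event reporting and harms {22} says "Patients in this trial are not having their care pathway altered in any way". Relevant concomitant care {11d} says "there will be no impact on concomitant or future care subsequent to the MDM presentation". Elsewhere the article says "Stratification into LA, BR and CR which determines optimal treatment" (Background {6a}) and "An increase in the diagnosed rate of BR disease to this level will result in more patients appropriately being given neoadjuvant therapy" (Sample size {14}). It lists as an outcome "To determine the change in the management strategies for patients with CR, BR and LA PDAC" (Table 1), and expects that better classification "may improve patient outcomes by avoiding ineffective surgery, optimising care and treatment planning" (Discussion).

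**The concern.** The resectability label is assigned after randomisation, and the intervention is designed to change it. Survival by phase within a label therefore compares groups that differ in composition, even if the report affects nobody's survival.

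The artefact can go either way. Suppose patients move from CR to BR and their prognosis lies between the two group means. Survival then rises in both groups, which looks like benefit. If patients move from LA to BR under the same condition, survival falls in both groups, which looks like harm. The Discussion describes patients who are misclassified and so miss curative options, which makes movement from LA at least as plausible as movement from CR. A real harm to movers could also be hidden.

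At stake is the reading of the secondary survival results. The primary outcome, its model and the randomisation are not affected.

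**Working it through.** **1. Share of the BR group that is relabelled (document figures only).** Take the same patient mix in both phases. If nobody leaves BR, the relabelled share of synoptic-phase BR patients is (15 − 8)/15 = 47%. If BR reaches only the pilot study's 13%, it is (13 − 8)/13 = 38%. Any movement out of BR raises these shares, so they are lower bounds.

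**2. Artefact with zero true effect.** The documents give no survival by category. Assumptions:
- survival at a fixed time: CR 80%, BR 65%, LA 45%
- shares of all patients under standard reporting: CR 16%, BR 8%, LA 16%
- movers' survival: 70% if from CR, 55% if from LA
- no individual's survival changes

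The new mean of a source group is (old share × old survival − moved share × movers' survival)/(remaining share). For BR the movers are added.

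| Source of the 7 points | CR | BR | LA | All non-metastatic |
|---|---|---|---|---|
| None | 80.0 | 65.0 | 45.0 | 63.0 |
| All from CR | (1280 − 490)/9 = 87.8 | (520 + 490)/15 = 67.3 | 45.0 | 63.0 |
| All from LA | 80.0 | (520 + 385)/15 = 60.3 | (720 − 385)/9 = 37.2 | 63.0 |
| 3.5 from each | (1280 − 245)/12.5 = 82.8 | (520 + 245 + 192.5)/15 = 63.8 | (720 − 192.5)/12.5 = 42.2 | 63.0 |

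The mixed move gives CR +2.8, BR −1.2 and LA −2.8. The one-way moves give CR +7.8 with BR +2.3, or LA −7.8 with BR −4.7. The pooled figure never moves.

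**3. Sensitivity of the one-way cases.**
- CR movers at 68% to 75%: CR +9.3 to +3.9, BR +1.4 to +4.7.
- LA movers at 50% to 60%: LA −3.9 to −11.7, BR −7.0 to −2.3.
- Source-group share 12% to 20%: CR +14.0 to +5.4, LA −14.0 to −5.4.
- A 5-point move (BR 13%): CR +4.5 and BR +1.9, or LA −4.5 and BR −3.8.

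**4. Masked harm.** Let the CR movers truly lose 3 points (70 to 67). CR still reads 87.8, and BR reads (520 + 469)/15 = 65.9. Both are up, although the true change over all patients is −0.07 × 3 = −0.21 points.

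**5. Precision of an all-patient comparison.** The variance calculation is generalised least squares with fixed period effects and discrete-time decay. As a check, it gives 83.9% power for the 40-hospital design with 15 patients per hospital-period, intracluster correlation 0.1 and autocorrelation 0.55; the article states 84%. For survival, assume 50% at a fixed time and 2400 patients, analysed as a risk difference.
- Ignoring clustering and period: SE = √(0.25 × 2/1200) = 2.0 points, 95% half-width 4.0.
- With 33 hospitals in batches of 12, 10 and 11, 2400/(33 × 6) = 12.1 patients per hospital-period and separate period effects per batch: SE 2.8 (half-width 5.5) at intracluster correlation 0.001, and SE 4.3 (half-width 8.5) at 0.1 with autocorrelation 0.55. The article states the latter pair for the BR outcome, not for survival.

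These figures only guide expectations for a Cox analysis; they are not its precision.

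**The case against.** The strongest reply is that no within-label survival contrast is explicitly planned. Other Table 1 rows, such as those for classification, neoadjuvant plans, margins and abandoned surgery, speak of a change, whereas the survival rows speak of a rate. The Cox sentence refers to one survival outcome and names no label stratum, so it may be meant as a pooled model. The choice of population could also be left to the statistical analysis plan.

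Much of this stands. A reader might infer that the protocol commits to testing survival between phases within each label; the text does not say so. What remains is that the only survival outcomes defined are label-specific, and that the general rule is to compare results between phases. An analysis plan can choose the model, but the outcome definitions are set in Table 1.

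It is also fair that the one-way cases are extremes. A reader might infer a known bias of 8 points, or a bias that flatters the synoptic report. Neither is supported: the survival values are assumed, and the mixed case gives about 3 points with opposite signs in CR and LA.

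On the care statements, the likely meaning is that the trial mandates no treatment. The text on discontinuation {11b} and post-trial care {30} supports this. A reader might infer that the report harms patients or that the consent waiver rested on this wording; nothing in the document shows either.

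**Conclusion.** The point holds in a limited form. Survival is defined only within labels that the intervention is designed to shift, and no label-independent survival population is given. Any within-label comparison by phase is therefore open to stage migration. From the article's own figures, at least 47% of synoptic-phase BR patients would be relabelled at the target, or 38% at the pilot rate. The resulting artefact is about 3 points in CR and LA for a mixed move and about 8 points for a one-way move. Both sizes rest on assumed survival and category shares. That the direction is unknown does not depend on those values.

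The conflict between the statements on care and the rationale is real as written, but it is a minor drafting matter that changes no result.

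**What to change.** 1. Make the between-phase survival comparison overall survival among all eligible patients regardless of category. Include metastatic patients: the synoptic report also records distant metastases, so a non-metastatic subset would still depend on the report.
2. Fit the Cox model with cluster frailty **and** the fixed effects for period within batch already specified for the other outcomes. With frailty alone, a stepped wedge comparison would exchange label bias for confounding by calendar time.
3. Report survival within CR, BR and LA descriptively only, and state that membership differs by phase.
4. Reword {11d} and {22}, for example: the trial mandates no treatment; the report may change the resectability label and, through it, treatment planning.

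The cost is one comparison on vital status that Table 3 already collects, plus a few sentences, all of which can be settled before the data are released. The downside is dilution and imprecision. Background {6a} puts half to two-thirds of patients as metastatic at diagnosis. With half-widths of roughly 5.5 to 8.5 points, the all-patient estimate removes the label bias but cannot detect or exclude small harms such as the 0.21-point example.
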